#### **(b) Research plan and methodology**

The aim of the study is two-fold: i) to evaluate the effects of a modelling-based narrative intervention on care-seeking beliefs, attitudes and knowledge, use of ambulance and prehospital care-seeking delays among AIM patients, and ii) to explore how and why the intervention affects the care-seeking behaviours from the patients' perspective. The behavioural intention, as reflected by the care-seeking beliefs and attitudes, are the primary outcomes, while AMI knowledge, use of ambulance and prehospital delays in care-seeking in AMI attacks are the secondary outcomes. The research hypothesis

of the first aim is that AMI patients who receive the modelling-based narrative intervention will report better changes in: i) care-seeking beliefs, ii) care-seeking attitudes, iii) AMI-related knowledge, iv) more likely to use ambulance, and v) shorter prehospital delays when AMI symptoms occur at 3, 12, and 24 months after the intervention, than those who receive didactic education on AMI care-seeking.

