### Study design

This is a sequential mixed-method study consisting of a randomised double-blind controlled trial and an exploratory qualitative study. The study implementation protocol is outlined in Figure 1. A research assistant (RA1) will recruit eligible participants from the cardiac clinics and wards of four regional hospitals in Hong Kong. The study sites are leading hospitals providing cardiac care services within the region. He/she will collect participants' baseline (T0) demographic data and study variables during a face-to-face interview. Block randomisation with a block size of 8, 10 or 12 will be used to ensure even distribution of participants between the two study groups. The block size and the respective allocation sequence to the intervention group receiving a modelling-based narrative intervention (by RA1) and control group receiving a didactic education (by RA2), will be determined by a computer-generated sequence. Participants chronologically recruited to the study will be allocated to the study groups by RA1 according to the computer generated sequence. Another independent RA (RA3), who is blinded to the study group allocation, will collect the post-intervention data. To detect short-term and long-term intervention effects, the outcome variables will be measured repeatedly at 3 (T1), 12 (T2) and 24 (T3) months following baseline data collection for both study groups. This extended period of outcome evaluation permits the study to detect the intervention effects on participants' actual care-seeking behaviours. Previous studies indicated that approximately 16% of these patients experienced AMI symptoms within two years. In the data collection telephone calls, the RA3 will enquire about whether the participants have been admitted to an emergency department with the experience of AMI symptoms. The study participants and their next of kin are strongly advised to contact the RA if they have been admitted due to a possible AMI attack.

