#### Outcome measures

The Acute Coronary Syndrome Response Index (ACSRI-C, Chinese version) will be used to measure the knowledge of AMI symptoms, care-seeking beliefs and attitudes upon symptoms occurrence. The knowledge subscale consists of 21 items to be responded dichotomously (yes/no). A four-point Likert scale is used to respond to the attitudes (5 items) and beliefs subscales (7 items). Higher scores indicate better knowledge, more appropriate care-seeking attitudes and beliefs. The ACSRI-C has good reliability (Cronbach's alpha = .81), convergent and construct validity.

The use of ambulance is defined as the primary means of selecting an ambulance as the transportation modality to hospitals. It will be retrieved from medical records and doubly confirmed with the participants.

The prehospital delay time is defined as the time interval between onset of acute symptoms and the documented time of arrival at a hospital's emergency department. The time of symptom onset will be elicited by patients' recall. To ensure its accuracy, a validated benchmarking technique in which the time of symptom onset is placed in the context of routine events that surround symptom onset will be used. The hospital arrival time will be retrieved from the patient's medical record.

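### Ambulance use and prehospital delay are tied to AMI attacks in one sentence and to unconfirmed AMI symptoms elsewhere, with no diagnosis collected, so a between-arm difference in non-AMI attendances could shift both outcomes in either direction.

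*Protocol*

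**What the plan says.** Four places in the protocol bear on which events count.

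- **Outcome sentence, section (b) Research plan and methodology:** "use of ambulance and prehospital delays in care-seeking in AMI attacks are the secondary outcomes".
- **Hypothesis, same section:** "shorter prehospital delays when AMI symptoms occur at 3, 12, and 24 months after the intervention".
- **Study design:** the blinded assistant asks by telephone "whether the participants have been admitted to an emergency department with the experience of AMI symptoms". Participants and relatives are "strongly advised to contact the RA if they have been admitted due to a possible AMI attack". The expected frequency is also symptom-based: "approximately 16% of these patients experienced AMI symptoms within two years".
- **Outcome measures:** delay is the "time interval between onset of acute symptoms and the documented time of arrival" at the emergency department. For transport, "The use of ambulance is defined as the primary means of selecting an ambulance as the transportation modality to hospitals". Transport mode and arrival time come from the medical record, but a diagnosis is not among the items collected.

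Under Study participants, a confirmed diagnosis is required only for the earlier AMI that makes a patient eligible. Data analysis adds no event definition.

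**The concern.** An AMI attack and an attendance with symptoms that might be AMI are different event sets, and the second contains the first. A participant can supply a value for ambulance use or delay only by attending hospital. Attendance happens after randomisation, and the intervention is meant to change it. The theoretical model behind it stresses susceptibility, alertness to atypical presentations and perceived severity. The sessions cover symptom recognition and transport, and the video ends with an emergency call.

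More attendances that turn out not to be AMI are therefore a foreseeable result. If they enter the analysis and their number differs between arms, the arms are compared on different mixes of events. A difference in median delay or ambulance share could then reflect case mix and not behaviour in a true attack. Without a recorded diagnosis the two explanations cannot be separated.

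**Working it through.** **1. Does any passage settle the event set?** The outcome sentence points to AMI attacks. The hypothesis, the telephone question, the self-report instruction and the anticipated rate all use symptoms or a possible attack. The definition of delay starts at symptom onset, which fits either set. The definition of ambulance use names no event and no denominator. No discharge diagnosis or adjudication is specified. The text does not settle it.

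**2. How many events are in play?** The sample size rests on the primary outcomes and plays no part here. It supplies only the arm sizes: 252 per arm and, allowing for 20% dropout, 252 / 0.80 = 315, as stated. At the protocol's 16%:

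- recruited: 0.16 × 315 = 50.4 per arm;
- after dropout: 0.16 × 252 = 40.3 per arm.

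These are counts on the symptom definition. Confirmed AMI would be fewer, by an amount the protocol does not give. With sets this small, a modest number of extra visits changes the mix.

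**3. Can case mix alone move the outcomes?** The protocol has no data on non-AMI attendances, so these inputs are assumptions:

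- true AMI in 8% of each arm, and non-AMI attendances in 8% of controls (together the 16%);
- non-AMI attendances in the intervention arm k times those in control, with k from 1 to 2;
- ambulance use of 50% in AMI (the Background reports non-use of up to 50%), and 65%, 50% or 35% in non-AMI;
- lognormal delay with log SD 1, median 3 h in AMI and 1.5, 3 or 6 h in non-AMI;
- no treatment effect within either event type.

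The AMI share of events is w = 8 / (8 + 8k) = 1 / (1 + k). Ambulance share = w × 0.50 + (1 − w) × p, where p is the non-AMI rate. The median t solves w·Φ(ln t − ln 3) + (1 − w)·Φ(ln t − ln m) = 0.5, where m is the non-AMI median.

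| k | w | Ambulance, p = 65% | p = 50% | p = 35% | Median, m = 1.5 h | m = 3 h | m = 6 h |
|---|---|---|---|---|---|---|---|
| 1 (control) | 0.50 | 57.5% | 50.0% | 42.5% | 2.12 h | 3.00 h | 4.24 h |
| 1.25 | 0.44 | 58.3% | 50.0% | 41.7% | 2.04 h | 3.00 h | 4.42 h |
| 1.5 | 0.40 | 59.0% | 50.0% | 41.0% | 1.97 h | 3.00 h | 4.56 h |
| 2 | 0.33 | 60.0% | 50.0% | 40.0% | 1.88 h | 3.00 h | 4.78 h |

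At k = 2 the ambulance share moves by +2.5, 0 or −2.5 points. The median moves by 1.88 − 2.12 = −0.24 h, by 0, or by 4.78 − 4.24 = +0.54 h. Restricted to true AMI, the arms are equal in every row.

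**The case against.** **Ascertainment wording.** Patients and relatives cannot be asked to report only confirmed infarctions, so a wide telephone question is compatible with an outcome restricted to AMI attacks. Delay has to start at symptoms under either definition. A reader might infer that the protocol counts every attendance a patient attributes to the heart. It does not say so; that reading comes from silence, and an SAP may define the analysis set. This much stands. But the hypothesis is not ascertainment wording, and an SAP can restrict to confirmed AMI only if the diagnosis is collected.

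**One arm only.** A reader might infer that only the narrative arm would generate false alarms. The control session also teaches the appropriate response to possible symptoms, so both arms may. What matters is a difference between arms, and its size is unknown.

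**Direction.** A reader might infer that extra visits must flatter the intervention. No figure in the protocol supports that. Its own rationale says atypical symptoms make evaluation harder and contribute to delay, which could point the other way.

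**A large effect.** One could take 40 true AMI events per arm at 50% ambulance use and add 20 non-AMI visits at 80% to the intervention arm alone, giving (20 + 16) / 60 = 60% against 50%. But 40 is 16% of 252 on the symptom definition, and the control arm is given no false alarms. Splitting 40 control events into 20 of each type at the same rates gives (10 + 16) / 40 = 65%. The intervention arm is then (10 + 24) / 50 = 68% if non-AMI visits rise by half, or (10 + 32) / 60 = 70% if they double.

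**Choice of event set.** Decisions are made before any diagnosis is known, so all symptom-prompted attendances are a defensible behavioural outcome. That is right, and it is a reason to report both sets.

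**Conclusion.** The point holds as an inconsistency in how two secondary outcomes are defined, joined to a gap in data collection. As written, the plan cannot isolate AMI attacks, and the set of attended events can be altered by the allocated intervention. The resulting bias may favour either arm or be absent. The figures in the table only show that case mix can act; they rest on assumed rates and are not estimates for this trial. Care-seeking beliefs and attitudes, the primary outcomes, do not depend on this event and are unaffected. The change is worth making because it is cheap, not because the trial's main result is at risk.

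**What to change.** - Use one event definition in section (b), Study design and Outcome measures. The telephone question can stay wide if it is described as the means of finding events.
- Abstract the discharge diagnosis from the medical record already opened for arrival time and transport mode.
- Report ambulance use and delay for record-confirmed AMI, which matches the outcome sentence, and for all suspected-AMI attendances, which matches the hypothesis. State in advance which of the two is the named secondary outcome.
- Report, by arm, the number of attendances and the proportion not confirmed as AMI, so that a change in case mix is visible.

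The cost is one extra field and consistent wording. The confirmed set will have fewer events and wider intervals. It also still conditions on an event after randomisation, so it removes the false-alarm route but is not a fully randomised comparison.

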### Study design

This is a sequential mixed-method study consisting of a randomised double-blind controlled trial and an exploratory qualitative study. The study implementation protocol is outlined in Figure 1. A research assistant (RA1) will recruit eligible participants from the cardiac clinics and wards of four regional hospitals in Hong Kong. The study sites are leading hospitals providing cardiac care services within the region. He/she will collect participants' baseline (T0) demographic data and study variables during a face-to-face interview. Block randomisation with a block size of 8, 10 or 12 will be used to ensure even distribution of participants between the two study groups. The block size and the respective allocation sequence to the intervention group receiving a modelling-based narrative intervention (by RA1) and control group receiving a didactic education (by RA2), will be determined by a computer-generated sequence. Participants chronologically recruited to the study will be allocated to the study groups by RA1 according to the computer generated sequence. Another independent RA (RA3), who is blinded to the study group allocation, will collect the post-intervention data. To detect short-term and long-term intervention effects, the outcome variables will be measured repeatedly at 3 (T1), 12 (T2) and 24 (T3) months following baseline data collection for both study groups. This extended period of outcome evaluation permits the study to detect the intervention effects on participants' actual care-seeking behaviours. Previous studies indicated that approximately 16% of these patients experienced AMI symptoms within two years. In the data collection telephone calls, the RA3 will enquire about whether the participants have been admitted to an emergency department with the experience of AMI symptoms. The study participants and their next of kin are strongly advised to contact the RA if they have been admitted due to a possible AMI attack.

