### (a) Background of research

#### The importance of timely care-seeking in the context of AMI

Acute myocardial infarction (AMI) is the acute and severe manifestation of coronary artery disease (CAD), resulting from a sudden cessation of coronary blood flow due to thrombotic occlusion. It is an emergency requiring immediate medical attention. The amount of myocardial necrosis from the moment of occlusion is curvilinear with a greater extent of cell death occurring in the early hours. In addition, the efficacies of reperfusion therapies are also highly time-dependent. Despite the types of reperfusion strategies, their efficacies diminish over time with a striking benefit observed within the first 2 hours of symptom onset. For instance, using an analysis of 22 trials, the researchers documented a substantial reduction in mortality when the thrombolytic drugs were administered within 2 hours of symptom onset. Likewise, De Luca et al. reported that the risk of 1-year mortality was raised by 7.5% for every 30-minute delay in receiving the percutaneous coronary intervention. Other than the ischaemic effect, AMI patients are prone to develop fatal arrhythmias in the early hours of disease onset. According to the latest statistics, majority of AMI-related deaths occur in the first hour of symptom onset are related to ischaemia-induced ventricular arrhythmias, which accounts for up to 70% of the CAD-related deaths. For this reason, early access to emergency medical care for prompt defibrillation and cardiopulmonary resuscitation is of paramount importance for AMI patients. Moreover, using ambulance for transporting to hospitals enables patients to get immediate emergency care from paramedic if fatal arrhythmia occurs. In Hong Kong, up to 50% of the patients did not use ambulance during an AMI attack, which greatly jeopardize their chance of survival. Indeed, AMI survivors are prone to have recurrent events and high mortality risk. A representative trial reported that up to 54% of patients presented with new myocardial ischaemia within the first year of AMI, while another large population trial showed a 17.4% of 1-year risk of re-infarction. Given that the time taken by patients to make their care-seeking decisions accounts for the major portion of the total ischaemic time and the high recurrent rates among the AMI survivors, there is a pressing need to develop effective interventions to promote timely care-seeking in AMI patients.

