### Study participants

Patients will be eligible to join the study if they are (1)  $\geq 18$  years of age, (2) living in the community, (3) with a confirmed diagnosis of a prior AMI attack, (4) consent to participate and (5) those who can read Chinese. Individuals who do not understand Cantonese, with impaired communication ability, psychiatric problems or impaired cognitive functioning (i.e. Abbreviated Mental Test  $\leq 6$ ) which may hinder participation in the interventional activities will be excluded. For the RCT study, the sample size is determined on the basis of a large-scale RCT examining the effect of a brief nursing educational intervention on care-seeking knowledge, attitudes and beliefs related to AMI in people with CAD. The effect sizes for knowledge, attitudes and beliefs were 0.39, 0.24 and 0.23 at 3 months after the intervention. In consideration of both clinical relevance and previous study findings, the sample size of this study is determined to give the study adequate power to detect at least a small to medium effect size on the primary outcomes. Using PASS 13 (NCSS, Kaysville, USA), it is estimated that a sample size of 252 subjects per study arm would give the study 80% power at 5%

level of significance to detect an effect size as small as 0.23 on our primary outcomes between the control and intervention arms at the post intervention time points. Further allowing for a potential dropout rate of up to 20%, a total of 315 subjects per arm will be recruited. For the qualitative phase, a criterion sampling of 30 participants who have received the modelling-based narrative intervention will be invited to join on the basis of their prehospital delay time, which will be categorised into three groups:  $\leq 2$  hours,  $> 2$  and  $\leq 6$  hours, and  $> 6$  hours. The criterion is set according to the international AMI management guidelines, where such cut-offs are used to categorise patients into early, intermediate and late responders. A total of 30 participants will be recruited, with 10 participants for each category. Maximum variations in the sociodemographic and clinical profile of the participants will also be adopted in the sampling procedure to illustrate a wider range of data.

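### Allocation is blocked but not stratified, so hospital and recruitment setting (ward or clinic) are balanced only by chance: a modest loss of precision, cheap to avoid

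*Protocol*

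**What the plan says.** Under Study design, a research assistant "will recruit eligible participants from the cardiac clinics and wards of four regional hospitals in Hong Kong". The allocation method is: "Block randomisation with a block size of 8, 10 or 12 will be used to ensure even distribution of participants between the two study groups". It is applied as follows: "Participants chronologically recruited to the study will be allocated to the study groups by RA1 according to the computer generated sequence". No separate list by hospital, setting or any other factor is mentioned, and the stated aim is equal numbers.

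Under Study participants, the clinical criterion is "with a confirmed diagnosis of a prior AMI attack", with no limit on how long ago. The criterion "living in the community" describes residence, so it does not exclude someone recruited while on a ward.

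Under Data analysis, the GEE models compare changes from T0 to T3 between arms. Baseline characteristics that differ between arms at p < 0.25 are considered as potential confounders. Hospital, setting and time since AMI are not named.

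**The concern.** Patients on a cardiac ward and patients attending a clinic, at four different hospitals, may differ in beliefs, attitudes and later events. The factors are known at enrolment, yet the allocation does not use them. When hospitals and settings recruit in parallel, consecutive places in a block go to patients from different strata, so blocking controls only the totals.

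Two things are at stake. Variation between hospitals and settings stays in the error term of the primary comparison unless the analysis removes it. And a visible imbalance at the end would have to be handled by a rule that looks at the observed imbalance and not at whether the factor predicts the outcome.

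**Working it through.** **Inputs.** From the protocol: 252 per arm evaluable, 20% dropout, 315 per arm recruited (630 in total), target effect size 0.23, two-sided 5% level, four hospitals, and about 16% expected to have AMI symptoms within two years. Assumed, because the protocol does not give them: half of participants recruited on wards, four hospitals of equal size, and a shift of 0.2 to 0.5 SD in the outcome between levels of the factor.

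**The plan's own figures.** 252 / (1 − 0.20) = 315, which reproduces. The standard two-group formula for 0.23 at 80% power gives 297 per arm, not 252; at 252 the power is Φ(0.23/√(2/252) − 1.96) = Φ(0.62) = 73.3%. That is a separate matter, but it is why the power figures below start from 73.3%.

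**Chance imbalance.** The standard error of the between-arm difference in a share p is √(2p(1 − p)/n).

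| Factor | n per arm | SE | 95% range |
|---|---|---|---|
| Setting, p = 0.50 | 315 | 0.0398 | ±7.8 points |
| One hospital, p = 0.25 | 315 | 0.0345 | ±6.8 points |
| Setting, p = 0.50 | 252 | 0.0445 | ±8.7 points |

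Simulating 10,000 unstratified 8/10/12 sequences for 630 patients, with settings and hospitals interleaved, gave ±7.9 and ±6.8 points. Arm totals never differed by more than 6. Blocking thus does its stated job and no more. If hospitals recruited one after another, hospital would be balanced within 0.8 points, but the protocol does not say that they do.

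**Effect on the primary outcomes.** Shift = imbalance × prognostic effect. At the 95% limit for 315 per arm: 0.078 × 0.2 = 0.016 SD and 0.078 × 0.5 = 0.039 SD. Against 0.23, that is 7% to 17%.

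**Power from adjustment.** A factor split 50/50 with effect d explains R² = d²/4 of the variance: 0.01 for d = 0.2 and 0.0625 for d = 0.5. The residual SD is √(1 − R²). Power at 252 per arm rises from 73.3% to 73.7% and 76.0% respectively, a gain of 0.4 to 2.7 points.

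**What the p < 0.25 rule catches.** The cut-off is z = 1.15. For p = 0.5 at 315 per arm it is reached at 1.15 × 0.0398 = 4.6 points. By construction, under randomisation a given factor misses this cut-off in 75% of trials, however prognostic it is. The shift left at the cut-off is 0.046 × 0.2 to 0.046 × 0.5, or about 0.009 to 0.023 SD.

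**The subset with later symptoms.** 0.16 × 315 ≈ 50 per arm. Without stratification the 95% imbalance is 1.96 × √(0.5/50) = ±20 points. With perfect stratification of all 315, it shrinks only by √(1 − 0.16) = 0.92, to about ±18 points. With event rates of 22% on wards and 10% in clinics (assumed), simulation gives ±18 and ±17.

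**What stratification does achieve.** Simulating eight lists (four equal hospitals × two settings), the 95% imbalance in setting among all 630 falls from ±7.9 to about ±1.3 points. The 95% limit for the difference in arm totals is then 8 participants.

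**The case against.** The strongest reply is that nothing here is an error. Unstratified blocks with 630 participants are valid, chance imbalance is already reflected in the standard errors, and the protocol promises only equal numbers. This stands: the point is one of efficiency, not validity.

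Next, the models compare changes from T0, so a difference in baseline level between ward and clinic patients drops out of the contrast. This also stands in large part. It makes the 0.016 to 0.039 SD an upper estimate, fully relevant only if the factor alters the course after baseline.

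Third, the p < 0.25 rule would bring in the larger imbalances if setting and hospital are recorded. It might, but it names neither and selects by imbalance instead of prognostic value. Nor can it see imbalance in the event subset, since it compares whole arms. The point cannot simply be left to a SAP: the protocol itself fixes both this rule and the allocation scheme.

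A reader might go further and infer three things that the documents do not support.

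- *That recent-AMI patients supply most of the ambulance and delay data.* The background reports that "up to 54% of patients presented with new myocardial ischaemia within the first year of AMI", and 17.4% re-infarction within a year, but gives no later-year comparator, and the figures come from other studies.
- *That ward recruitment is the best marker of recency.* The protocol ranks no markers, and a ward patient with an old AMI may be admitted for another reason.
- *That stratifying would repair the ambulance and delay comparisons.* The calculation above shows that it barely changes balance there.

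**Conclusion.** The point holds as a modest and inexpensive improvement. Hospital and setting are left to chance, with a 95% range of about ±7 to ±8 points at 630, and the planned analysis does not guarantee that either is adjusted for. There is no bias. At the 95% limit the primary-outcome difference moves by about 0.016 to 0.039 SD, and adjustment is worth 0.4 to 2.7 points of power. These figures rest on an assumed 50% ward share, an assumed prognostic effect of 0.2 to 0.5 SD, and hospitals and settings recruiting in parallel.

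The absence of a limit on time since AMI is not itself a fault and needs no change in eligibility. Stratifying by setting would not balance time since AMI among clinic patients; recording it and adjusting for it is the direct route.

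**What to change.** - **Study design:** generate separate permuted-block lists by hospital and recruitment setting (4 × 2 = 8), keeping block sizes 8, 10 and 12. This has to be done before allocation starts, because it cannot be applied to patients already allocated.
- **Data analysis:** enter hospital and setting as prespecified covariates in the primary-outcome models, whatever their baseline p-value.
- **Baseline (T0) data:** record the date of the most recent AMI, so that time since AMI can also be a prespecified covariate and be described by arm.
- **Ambulance use and prehospital delay:** use the same covariates only as far as the number of events allows. With about 50 events per arm, a model with every hospital, setting and recency term may be too large.

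**Cost:** eight lists in place of one, up to eight unfinished blocks at the end (arm totals differing by a few participants), and one extra date field. No extra patients are needed and eligibility is unchanged.

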### Study interventions

**The modelling-based narrative intervention** will adopt an eclectic approach that integrate behavioural modelling and a narrative approach to promote knowledge and skill internalisation and retention (Table 1). The intervention will offer a vivid decision making experience to the participants. Participants of the intervention group will receive a modelling-based narrative intervention to be delivered by RA1. He/she will receive 3-days of intensive training from the investigation team on AMI management and care-seeking, principles and skills of group facilitation and counselling, and the ways of delivering the study protocol, accordingly.

The 7-week intervention consists of three weekly 90-minute face-to-face sessions in a small group of 6-8 participants, followed by a half-day booster session one month after the three weekly sessions (Figure 2). The small group format is adopted because it is effective in providing peer support and facilitating peer learning. Each of the face-to-face sessions will begin with a brief educational presentation on a relevant topic by the intervener. These weekly topics are coherent with the critical junctures that people commonly encounter when they make care-seeking decisions in the context of AMI. They include: (1) symptom recognition and risk identification, (2) emotional response to possible AMI attack and perceived barriers and facilitators to care-seeking, and (3) means of care-seeking and transportation. To optimise the effects of teaching and learning, coloured pictures and interactive skills will be used to illustrate the health information. Emphasis will be placed on enhancing patients' understanding of the symptom manifestations, disease pathophysiology, nature of disease progression, principle of treatments, appropriate care-seeking behaviours and realising the significance of their prompt care-seeking behaviours in making a difference to their health outcomes. The education content of each session complies with the latest international practice guidelines and recommendations published by the European Society of Cardiology and American Heart Association. The content has been validated by a panel of experts, including cardiologists, advanced practice nurses and nursing academicians in cardiac care.

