**A didactic education on AMI care-seeking** will serve as the **control intervention**. It consists of one session to be delivered in a small group (6–8 participants/group) format by another RA (RA2). The factual information about AMI and the appropriate response towards possible symptoms will be delivered with a structured PowerPoint slide-set. Narrative approach and booster sessions will not be used in the control group. The intervener will answer questions from the participants when asked, according to the structured education content for the control group. The questions and topics discussed will be recorded for subsequent data interpretation. During the conversation, the RA will not use any wordings which is related to patient's privacy (e.g. patient's name, address etc.) and will only use a subject code to label all the audio records. Permission of audio recording of the conversation will be obtained in the informed consent and before the start of the conversation as well.

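### One research assistant recruits, takes baseline, allocates and delivers the experimental arm with no concealment step described, and the double-blind label is unsupported

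*Protocol*

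**What the plan says.** The Protocol's Study design section introduces "a randomised double-blind controlled trial" and then assigns the tasks.

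- Recruitment: "A research assistant (RA1) will recruit eligible participants from the cardiac clinics and wards of four regional hospitals in Hong Kong".
- Baseline: "He/she will collect participants' baseline (T0) demographic data and study variables during a face-to-face interview". The pronoun refers back to RA1.
- Allocation: "Participants chronologically recruited to the study will be allocated to the study groups by RA1 according to the computer generated sequence". The sequence is computer-generated in permuted blocks of 8, 10 or 12.
- Follow-up: an independent assistant, RA3, blinded to allocation, collects the post-intervention data at 3, 12 and 24 months (T1 to T3).

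The Study interventions section adds the delivery roles. "Participants of the intervention group will receive a modelling-based narrative intervention to be delivered by RA1", as three weekly 90-minute group sessions and a half-day booster. The control arm is a single didactic group session given by RA2, and "Narrative approach and booster sessions will not be used in the control group".

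The primary outcomes are care-seeking beliefs and attitudes, which participants rate on four-point items (Outcome measures). The Data analysis section compares differential changes from T0 to T3 between arms by GEE.

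**The concern.** Randomisation protects against selection only if the person enrolling a patient cannot foresee the arm. Here the enroller also applies the sequence and then runs one of the two arms, so RA1 has a stake in who joins those groups. With foreknowledge, RA1 could approach or encourage some patients and not others according to the arm that comes next. RA1 could also, without intending to, prompt differently in the face-to-face T0 interview.

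The second route matters because of how measurement is divided. RA3's blinding covers T1 to T3. The T0 belief and attitude scores are the only ones taken by someone who may know the arm, and they are the reference point for the change analysis.

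The blinding label is a separate matter. Calling the trial double-blind tells readers that self-reported outcomes are protected from participants' knowledge of their arm, and the text describes no such protection.

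**Working it through.** The plan states no figure on this point, so there is none to reproduce. The check traces the roles first and then sizes the consequences.

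**1. Roles side by side**

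| Task | Who | Protocol section |
|---|---|---|
| Recruits | RA1 | Study design |
| T0 interview | RA1 | Study design |
| Applies the sequence | RA1 | Study design |
| Delivers experimental arm | RA1 | Study design; Study interventions |
| Delivers control arm | RA2 | Study design; Study interventions |
| Collects T1 to T3 | RA3, blinded | Study design |

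The text mentions no central release, sealed envelopes or independent list holder. It describes recruitment and T0 before randomisation, but that order alone is no barrier when one person does all three.

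**2. Predictability if upcoming assignments were sealed**

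RA1 makes the allocations and so knows the past ones. Suppose RA1 always guesses the arm that is behind, and tosses a coin when the arms are level. For a 1:1 block of size b = 2m, the expected number of correct guesses is m + (4^m / C(2m, m) − 1)/2.

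| b | Expected correct guesses | Share |
|---|---|---|
| 8 | 4 + (256/70 − 1)/2 = 5.329 | 66.6% |
| 10 | 5 + (1024/252 − 1)/2 = 6.532 | 65.3% |
| 12 | 6 + (4096/924 − 1)/2 = 7.717 | 64.3% |

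If the three sizes are equally likely, the mixed share is (5.329 + 6.532 + 7.717)/(8 + 10 + 12) = 19.58/30, or about 65%. A simulation over 630 patients (315 per arm) gave 65.2%. Every block ends balanced, so the rule needs only the running difference between arms. It works without knowing which block size is in use, and varying the size is therefore no substitute for concealment.

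**3. What a T0 distortion would do**

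The contrast is (follow-up − T0) in the intervention arm minus the same in the control arm. If T0 is elicited δ lower in the intervention arm and the distortion does not persist to follow-up, the contrast shifts by +δ. A distortion the other way shifts it by −δ. The Protocol gives no basis for δ. As an illustrative assumption, against the 0.23 effect size in the Study participants section:

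- δ = 0.05 SD: 0.05/0.23 = 22%
- δ = 0.10 SD: 0.10/0.23 = 43%

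**4. Who is blinded**

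RA1 and RA2 know the arm because they deliver it. Participants attend either three sessions and a booster or one lecture, and no masking of them is described. That leaves RA3 as the only party stated to be blinded.

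**The case against.** The strongest reply is that the Protocol never says RA1 sees upcoming assignments. It does not state who generates or holds the sequence or when each assignment is revealed, and the implementation figure is not available. That is right. A reader might infer that all 630 assignments are open to the recruiter, but this would hold only if RA1 has the list, which the text neither says nor rules out. What stands is that the enroller is named as the allocator and no barrier is described. Because the Protocol fixes who allocates, this is more than a detail left to another document.

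A second reply concerns the mechanism. A reader might infer that any T0 imbalance passes straight into the treatment effect and that no adjustment can remove it. That is too broad. If selective enrolment produces a true and stable baseline difference, it largely cancels in a change comparison. Using T0 as a covariate would shrink a measurement distortion in proportion to the T0-to-follow-up slope, and a follow-up-only comparison would avoid it. RA1 also does not rate patients; they answer fixed items, so the risk is prompting rather than scoring. What remains is non-persisting T0 distortion under the planned analysis, and selection on traits such as motivation that could alter response. The planned adjustment for baseline characteristics with p below 0.25 reaches only what is measured.

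Third, RA3's blinding is real and covers all post-intervention data collection. Both arms receive small-group education, and the consent pages are not available, so masking of participants to the hypothesis cannot be excluded. The text does not claim it, however, and the interveners cannot be blind.

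**Conclusion.** The point holds in two parts.

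**Allocation.** RA1 enrols, interviews at T0, applies the sequence and delivers the experimental arm, with no concealment step described. The allocation procedure as written is therefore open to selection and to arm-dependent prompting. Predictability is about 65% if upcoming assignments are sealed, assuming equally likely block sizes and guessing from past allocations. It would be complete only if RA1 holds the list, which the documents do not establish. The resulting bias is of unknown size and direction; the 22% to 43% range illustrates assumed distortions and is not an estimate.

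**Blinding.** The single use of double-blind, in the Study design section, is not supported by the design described. It would be wrong to conclude that the trial has no blinding, because assessor blinding is stated. This part is a labelling correction and changes no procedure.

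**What to change.** 1. In the Study design section, name an existing team member who does not recruit, deliver or assess outcomes as holder of the sequence. Each assignment should be released, by sequentially numbered opaque sealed envelope or web form, only after consent and after T0 data are completed and locked. RA1 should be given neither the list nor the block size in use.
2. Replace the double-blind label in that section with *outcome-assessor-blinded*.

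The cost is a small administrative step per enrolment and two wording changes. Some predictability remains while RA1 both recruits and delivers, because RA1 will still learn past assignments; the guessing rule in the working does not depend on block size. Recording RA3's guess of the arm at follow-up is optional good practice and not part of the correction.
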